# Phototherapy Using a Light-Emitting Fabric (BUBOLight) Device in the Treatment of Newborn Jaundice: Protocol for an Interventional Feasibility and Safety Study

**DOI:** 10.2196/24808

**Published:** 2021-05-25

**Keywords:** jaundice, light emitting fabrics, light, neonate, newborn jaundice, perinatal, phototherapy

## Abstract

**Background:**

Neonatal jaundice is a common condition occurring in 60%-80% of all healthy-term and late-preterm neonates. In the majority of cases, neonatal jaundice resolves spontaneously and causes no harm; however, in some neonates, signiﬁcant hyperbilirubinemia can develop and lead to kernicterus jaundice, a serious neurological disease. Phototherapy (PT) is the preferred treatment for jaundice; however, to be effective, PT devices need to have a broad light emission surface to generate no or little heat and to provide an optimal wavelength and light intensity (420-490 nm and ≥30 µW/cm²/nm, respectively).

**Objective:**

This study aimed to investigate the feasibility, safety, and level of satisfaction of parents and health care teams with the BUBOlight device, an innovative alternative to conventional hospital PT, in which luminous textiles have been incorporated in a sleeping bag.

**Methods:**

This interventional, exploratory, simple group, nonrandomized, single-center trial will be conducted at Lille Hospital. In total, 10-15 neonates and their parents will be included to obtain evaluable data from 10 parent-neonate pairs. Neonates weighing more than 2500 g at birth and born with ≥37 weeks of amenorrhea that required PT in accordance with the guidelines of the National Institute For Health and Clinical Excellence will receive one 4-hour session of illumination. Total serum bilirubin and transcutaneous bilirubin levels were obtained at the start and 2 hours after the end of PT. Cutaneous and rectal temperatures, heart rate, and oxygen saturation will be measured at the beginning and during PT. The number of subjects is therefore not calculated on the basis of statistical assumptions. We aim to obtain a minimum proportion of 90% (ie, 9 of 10) of the neonates included, who have been able to undergo 4-hour PT without unacceptable and unexpected toxicities. We will calculate the mean, median, quartiles, minimum and maximum values of the quantitative parameters, and the frequency of the qualitative parameters. The rate of patients with no unacceptable and unexpected toxicities (ie, the primary endpoint) will be calculated.

**Results:**

The first patient is expected to be enrolled at the end of 2020, and clinical investigations are intended for up to June 2021. The final results of this study are expected to be available at the end of 2021.

**Conclusions:**

Our findings will provide insights into the safety and feasibility of a new PT device based on light-emitting fabrics for the treatment of newborn jaundice. This new system, if proven effective, will improve the humanization of neonatal care and help avoid mother-child separation.

**Trial Registration:**

ClinicalTrials.gov NCT04365998; https://clinicaltrials.gov/ct2/show/NCT04365998

**International Registered Report Identifier (IRRID):**

PRR1-10.2196/24808

## Introduction

Neonatal jaundice or hyperbilirubinemia is very common in neonatology. Neonatal livers are generally immature, and this condition leads to poor metabolism of bilirubin. Bilirubin is not sufficiently degraded and accumulates excessively in the blood. This clinically manifests as yellowing of the skin and mucous membranes. Based on etiology, jaundice can be divided into physiological and pathological jaundice [1,2].

The evolution of pathological jaundice is often favorable, but it can lead to complications such as acute or even chronic encephalopathy known as kernicterus [3].

Hyperbilirubinemia from any cause among healthy infants is considered to be of concern if the bilirubin level is >18 mg/dL (>308 μmol/L) in infants who are 49-72 hours old [4] and requires prompt management. Furthermore, jaundice is the primary cause of rehospitalization in the first 15 days of life, which makes it an important issue for health professionals.

Screening and diagnosis of jaundice is routinely performed for all neonates. It is based on a daily visual clinical assessment, which must be combined with a transcutaneous bilirubin measurement or total serum bilirubin measurement as only 50% of neonates with a total serum bilirubin concentration of >128 μmol/L visually appear to have jaundice, especially dark-skinned neonates [5].

Bilirubin is a yellow pigment that preferentially absorbs blue, violet, or green light (400-490 nm) [6]. Phototherapy (PT) is used as first-line treatment for hyperbilirubinemia. The aim of PT is to decrease or prevent an increase in the concentration of circulating bilirubin by using blue light.

Light absorption by bilirubin induces the formation of photoisomers that can be excreted in the urine or bile, thus bypassing hepatic conjugation [7,8].

The indication for PT depends on the total bilirubin levels in blood and the presence or absence of conditions that increase the risk of bilirubin neurotoxicity.

Intensive PT, defined by an irradiance of ≥30 µW/cm^2^/nm, is more effective than conventional PT [9], but there is no standardized method for delivering efficient PT. Nonetheless, PT for a short duration (ie, 4 hours) by illuminating the largest body surface bas been recommended [10].

There are several PT devices that contain light-emitting diode–based lights, conventional fluorescent blue lights, or conventional halogen lights with an emission spectrum of 420-490 nm, which can provide effective irradiance to reduce serum bilirubin levels [11], but characteristics such as the distance of the light source from the neonate, the area illuminated, and the irradiance affect the effectiveness of phototherapy [12].

The BUBOLight PT device is composed of a light source and light-emitting fabrics (LEFs) in a sleeping bag. LEFs incorporate optical fibers inside a textile structure. By controlling the density of the fibers and the bending angles, this structure makes it possible to obtain a homogeneous light distribution on a very flexible textile surface.

BUBOLight emits light with a wavelength of 445 nm, an irradiance equal to 3.5 mW/cm², and a useful surface of 756 cm². It thus has the characteristics of an effective PT; that is, a sufficiently exposed surface, a wavelength similar to the maximum absorption peak of bilirubin, a sufficiently high irradiance, bilateral illumination to increase the total treatment surface, and a homogeneous and stable light distribution.

In addition, BUBOLight has been designed not to heat up, thus avoiding the risk of hyperthermia in neonates. When used in the infant's bed, it helps preserve parent-child interactions and does not require the wearing of protective glasses because the light cannot pass through the sleeping bag. Finally, the infant is installed with a special diaper that includes protection for the genitals. The aim of the present protocol is to evaluate the feasibility and the safety of the BUBOLight device as a new PT method.

## Methods

### Trial Design

This interventional, exploratory, simple group, nonrandomized, single-center study will include 10-15 neonates in order to obtain evaluable data from 10 parent-child pairs.

### Setting

The study will be conducted at the department of obstetrics at Lille University Hospital (Lille, France), over a period of 6 months until June 2021. Parent-neonate couples will be included and followed-up in the study until neonatal serum bilirubin levels are measured 2 hours after the end of PT. The participation of parent-child pairs in this study will then be limited to a 6-hour session.

### Device

The complete BUBOLight device consists of an electrically powered light source that emits blue radiation with a predefined wavelength of 445 nm connected to an active textile part (Figure 1). The active textile part of the device consists of sleeping bag system in which are integrated 2 removable LEFS (Figure 2) to diffuse a blue light from a light source. The light source was designed by the ONCO-THAI U1189 (Lille, France) and is composed of 2 light sources with an output power of 4 W. The active textile part (MDB Texinov) has a usable surface area of 756 cm² and can deliver an irradiance of 3.5 mW/cm² (with a variation of 20%) in blue light.

**Figure 1 figure1:**
[figure not shown]
Complete device and light source.

**Figure 2 figure2:**
[figure not shown]
Light-emitting fabrics in the sleeping bag.

### Participants

To be eligible for the study, neonates must meet all the inclusion criteria described in Textbox 1. Neonates must not meet any of the exclusion criteria.

Inclusion and exclusion criteria.
**Inclusion criteria**
Infants born at the Lille University Hospital and not out of this hospitalGestational age of ≥37 weeks with amenorrhea Presence of jaundice confirmed through transcutaneous bilirubin measurement with a bilirubinometer (model JM-105, Dräger) (Reference graphs related to gestational age–specific thresholds for initiating PT treatment [13])Rate of total serum bilirubinemia requiring phototherapy (Reference graphs related to gestational age–specific thresholds for initiating PT treatment [13])Absence of rhesus or Kell fetal-maternal incompatibilityWeight at birth of ≥2.5 kgDiscerned to be in good health by the investigator after clinical examination and on the basis of medical data (absence of perinatal asphyxia, antibiotic treatment, and respiratory disorders)
**Exclusion criteria**
Neonate who has already been treated with PTFebrile state with a body temperature of >37.5°CTotal bilirubinemia rate or excess of 100 µmol/L as an indication for PTNeonates with jaundice due to hemolysis or functional or anatomical obstructionWeight loss of >10% of the birth weightNeonates requiring treatment other than PTNeonates with congenital erythropoietic porphyria or a family history of porphyria.Presence of ≥2 of the following risk factors:Gestational age of <38 weeks of amenorrhea Icterus of the first 24 hoursABO incompatibilityPositive irregular agglutinin test status of the motherHistory of jaundice treated in siblingsHistory of familial hemolysisSerosanguineous bump, bruise, cephalohematomaIneffective breastfeedingWeight loss of ≥8%Parents who are noncompliant with the study design

### Study Objectives and Outcomes

The primary objective of the study is to evaluate the safety of the BUBOLight PT device as an alternative to conventional tunnel PT under the usual conditions for the management of jaundice in neonates.

Safety will be based on the proportion of neonates who received complete and effective 4-hour PT with the BUBOlight device and did not experience unacceptable and unexpected toxicities (target set at least 90% of neonates).

The key secondary objectives are the individually frequency of each adverse effect, monitoring of serum bilirubin and transcutaneous levels under phototherapy, and the perceptions of parents and health team with the use of the device (comfort, heat, humidity, ease of breastfeeding, proximity, and possibility of contact with the baby) and causes of PT discontinuation. Table 1 summarizes the study objectives and outcomes.

**Table 1 table1:** Study objectives and outcomes.

Outcomes		Inclusion: initiation of phototherapy (hour 0)	1 hour after the beginning of phototherapy	2 hours after the beginning of phototherapy	4-hour effective phototherapy	2 hours after the end of phototherapy

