**Primary outcomes: safety**						
	Monitoring of hyperthermia (body temperature of ≥38°C) or hypothermia (body temperature of ≤36°C)	✓	✓	✓	✓	
	Oxygen saturation of <90% for >15 seconds	✓	✓	✓	✓	
	Heart rate of >160 beats/minute during inactivity or <80 beats/minute for >15 seconds	✓	✓	✓	✓	
	Allergic contact reaction of grade ≥3 (Ring and Messmer classification [14])	✓	✓	✓	✓	

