**Secondary outcomes**						
	Description of the number of neonates presenting each adverse event individually (skin lesion, dehydration, diarrhea, etc)	✓	✓	✓	✓	
	Monitoring of serum bilirubin levels	✓				✓
	Monitoring of transcutaneous bilirubin levels	✓				✓
	Evolution of the EDIN^a^ score: neonatal pain and discomfort scale	✓			✓	
	Number of feedings, number of diaper changes and the causes of cessation of phototherapy			✓	✓	
	Perceptions of the parents with the use of the device and interaction with their child					✓

^a^EDIN: Échelle de Douleur et d'Inconfort du Nouveau-né.

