### Sample Size

This is a pilot feasibility study. The number of subjects is therefore not calculated on the basis of statistical assumptions. We propose to include 10-15 neonates and their parents in order to obtain evaluable data from 10 parent-neonate pairs. The feasibility objective is to obtain a minimum proportion of 90% (ie, 9 of 10) of the neonates included in this study, having undergone PT without unacceptable and unexpected toxicities.

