### Intervention

Neonates who have not been discharged from the hospital and who require PT for jaundice will be included in the study after verification of the inclusion and exclusion criteria.

As shown in Figure 3, parent-neonate pairs who meet all of the inclusion criteria and none of the exclusion criteria are invited to participate in the study, which will involve a single visit.

The study will include an effective 4-hour PT session (which may be discontinued for a few minutes to change diapers if necessary) followed by a 2-hour rest period in accordance with the recommendations of the French National Reference Center for Perinatal Hemobiology. Serum bilirubin levels will be determined upon initiation of PT (H0) and 2 hours after the effective end of PT; that is, at approximately H0+6 hours, in order to check for a reduction in bilirubin levels. Transcutaneous measurement with a bilirubinometer (Dräger Jaundice Meter JM-105) will be also performed upon initiation of PT and 2 hours after the effective end of PT.

Heart rate and oxygen saturation will be continuously recorded using a monitor, which is usually used during PT. Alarms will be set to detect desaturation and bradycardia episodes lasting >15 seconds. The investigator will check the scope at the end of the monitoring period for false episodes related to an artefact.

In addition, axillary and cutaneous temperatures will be regularly monitored in order to prevent any risk of dehydration and hyperthermia. Room temperature will also be measured.

The neonatal pain and discomfort scale (Échelle de Douleur et d'Inconfort du Nouveau-né [EDIN] score) and the opinion of parents and health professionals on the use of the device will also be sought.

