### Statistical Analysis

Security and acceptability will be assessed using descriptive data. All data will be described individually and summarized using the following statistical parameters:

*Primary objective:* the mean, median, quartiles, minimum and maximum values of the quantitative parameters, and the frequency of the qualitative parameters will be calculated. The rate of patients with no unacceptable and unexpected toxicities (primary endpoint) will be calculated.

*Secondary objectives:* bilirubin levels and EDIN score data for neonatal pain and discomfort will be expressed as means, medians, quartiles, and minimum and maximum values at each measurement time.

Changes in serum and transcutaneous bilirubin levels among PT initiation (H0), H0+4 hours (only transcutaneous), and 2 hours after the end of PT, and changes in the EDIN score between PT initiation (H0) and after 4 hours of actual treatment will also be described. Furthermore, we will calculate the mean, median, quartiles, minimum and maximum values of the quantitative parameters (number of feedings, diaper changes, and care), and the frequency of the qualitative parameters (perceptions of the parents and the health team regarding the use of the device and interaction with their infant).

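### The primary safety endpoint is worded as freedom from toxicity that is both unacceptable and unexpected, but Table 1 lists four thresholded events as primary, and nothing makes the two the same definition

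*Protocol article*

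**What the plan says.** **Worded endpoint.** Study Objectives and Outcomes counts a neonate as a success if the 4-hour phototherapy was complete and effective and the neonate "did not experience unacceptable and unexpected toxicities (target set at least 90% of neonates". The Abstract and Sample Size use the same pair of adjectives. Statistical Analysis repeats them as the quantity to be computed: "The rate of patients with no unacceptable and unexpected toxicities (primary endpoint) will be calculated". That sentence mentions neither Table 1 nor completion of the session.

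**Target.** Sample Size states: "The feasibility objective is to obtain a minimum proportion of 90% (ie, 9 of 10) of the neonates included in this study". It also says "The number of subjects is therefore not calculated on the basis of statistical assumptions".

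**Table 1, primary block.** Four rows stand under primary safety outcomes. The first is "Monitoring of hyperthermia (body temperature of ≥38°C) or hypothermia (body temperature of ≤36°C"; the others are an oxygen saturation limit, heart rate limits, and an allergic contact reaction of grade 3 or more. None refers to expectedness.

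**Table 1, secondary block.** All other adverse events fall under "Description of the number of neonates presenting each adverse event individually (skin lesion, dehydration, diarrhea, etc", with no severity threshold.

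**Foreseen risk.** Intervention says that temperatures will be "regularly monitored in order to prevent any risk of dehydration and hyperthermia". The Introduction also names hyperthermia, as a risk that the device is designed to avoid.

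**The concern.** The wording and the table need not count the same neonates as failures.

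- Because the two adjectives are joined by *and*, an event that is unacceptable but foreseen is not a failure. Hyperthermia is foreseen in the protocol's own text, yet it is the first primary row of Table 1.
- If Table 1 is taken as the definition, that gap closes and another opens. A serious adverse event outside the four rows does not reduce the primary safety rate as long as the session is completed.

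Safety is the primary objective, and the single figure reported for it is compared with a target. The study is analysed without blinding. Undefined adjectives would leave the classification of an event to judgement after it is known.

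**Working it through.** **1. The plan's own figure.** 9/10 = 0.90, so the target allows one failure in 10. Sample Size says "We propose to include 10-15 neonates and their parents in order to obtain evaluable data from 10 parent-neonate pairs", so the denominator could be larger if all included neonates count. The smallest whole number at or above 0.9n is 9, 10, 11, 12, 13 and 14 for n = 10 to 15. That is one failure allowed at every size. Two failures miss the target even at n = 15: 13/15 = 86.7%.

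**2. Two neonates in 10 reach 38°C; all complete the session; nothing else occurs.**

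| Definition of failure | Failures | Success rate | Target of 90% |
|---|---|---|---|
| Any Table 1 primary event | 2 | 8/10 = 80% | missed |
| Literal wording, hyperthermia taken as expected | 0 | 10/10 = 100% | met |

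**3. One or more neonates have a serious event outside the four rows** (for example a severe non-allergic skin lesion) **and complete the session.** If Table 1 is the definition, no primary row is met and completion is satisfied, so each counts as a success. With two such neonates in 10 and no other event, the rate is 10/10. The lesion appears only in the secondary tabulation.

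**4. How often the first gap could matter.** The article gives no event risks, so these are assumptions. Let q be the risk per neonate of a foreseen Table 1 event, with p = 1 − q. Then P(at least 9 of 10 successes) = 10·p⁹·q + p¹⁰.

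- q = 5%: 0.3151 + 0.5987 = 0.914
- q = 10%: 0.3874 + 0.3487 = 0.736
- q = 20%: 0.2684 + 0.1074 = 0.376

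If the literal wording never counts these events and nothing else happens, the corresponding probability is 1 throughout.

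**5. Completion.** Study Objectives and Outcomes makes a complete, effective 4-hour session part of success, and the Abstract's target also refers to undergoing it. The endpoint sentence in Statistical Analysis does not. A harm that ends the session is therefore a failure under the first section, but not necessarily under the sentence that computes the rate.

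**The case against.** The strongest reply is that Table 1 is simply the operational form of the phrase. Study Objectives and Outcomes states the endpoint and then points to Table 1 as a summary of outcomes, and there is no other list of primary events. An analyst who scored 38°C as a success would have to ignore a row labelled primary. This is plausible and may be what was meant. The article does not say it, however, Statistical Analysis repeats the phrase without the list, and this reading still leaves serious unlisted events outside the rate.

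Several stronger readings are tempting and are not supported:

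- *All four primary rows are expected events.* Only hyperthermia is named as a risk. For desaturation and bradycardia this is inferred from alarm settings. For hypothermia, tachycardia and contact allergy it rests only on their being listed. Monitoring for an event does not make it expected, and a device designed not to heat could make even hyperthermia arguably unexpected.
- *Two serious skin injuries give 8/10 under the wording and 10/10 under Table 1, a flip in the opposite direction.* Skin lesion is itself listed in advance in the secondary block. If listing makes an event expected, the wording gives 10/10 as well and nothing flips.
- *The secondary row bars its events from the primary rate.* It asks for a count of each event and does not exclude dual counting. Nothing provides for it either.
- *Any burn would be counted as a success.* One that ends the session already fails the completion requirement in Study Objectives and Outcomes.

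It is also fair that this is an exploratory single-group pilot in which all data are to be described individually, so no harm would go unreported. A condensed article may leave definitions to the full protocol. That does not cover a stated rule and a stated table that can give different counts.

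**Conclusion.** The point stands as a defect in the definition of the primary endpoint. The stated rule can drop unacceptable but foreseen harms from the safety rate, and Table 1 used as the definition omits serious harms outside its four rows that do not stop the session. The demonstrated size is a change from 8/10 to 10/10 across the 90% line when two neonates become hyperthermic. This rests on the literal reading of the wording and on treating hyperthermia as foreseen, which the Introduction and Intervention support. The probabilities above are illustrations under assumed risks. No sample size, power or error rate is affected, since none is calculated. In a descriptive pilot with individual reporting, this is a cheap correction to make before analysis and not a must-fix.

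**What to change.** Use one definition of failure in the Abstract, Study Objectives and Outcomes, Table 1, Sample Size and Statistical Analysis. A neonate fails if any of these occurs:

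1. any Table 1 primary event, whether expected or not;
2. any other serious adverse event;
3. the effective 4-hour session is not completed, which is already required in Study Objectives and Outcomes and should be added to Statistical Analysis.

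Remove expectedness from the endpoint. Keep the individual adverse event counts as a secondary outcome, and say that an event counted there may also be a primary failure.

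The cost is wording only, because adverse events are already collected. The observed success rate may be slightly lower. As an illustration with assumed, independent risks of 10% for a Table 1 event and 2% for another serious event, p = 0.90 × 0.98 = 0.882, and the chance of at least 9 of 10 falls from 0.736 on the Table 1 list alone to 0.666, before counting incomplete sessions.
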